### Interventions

2.10

Participants will receive 6 sessions of treatment over 8 weeks (every 1–2 weeks per session). Each session will last for 30 minutes. Trained and experienced TCM practitioners or physiotherapists who have studied massage and must have received professional training and passed a test to ensure consistency of study methods before participating in the trial will provide the treatment. (Appendix 1).

### Outcome measurements

2.11

The primary outcome measure assesses the efficacy of massage therapy for the treatment of CNLBP: change in low back pain measured by the 100 mm VAS^[31]^ over the 2-month treatment. Secondary outcome measures included the Oswestry Disability Index^[32]^ (ODI), spinal range of motion^[33]^ (ROM), and the 36-item short-form health survey^[34]^ (SF-36). Fig. 2 demonstrates all measurements and measuring time points.

### Safety evaluation

2.12

Since TN and PT are both non-invasive external treatments, the side effects are minor, but in the course of operation, if the technique is misused, there may be accidents such as muscle, bone, or joint damage of the spine or other parts of the body. Therefore, the response to an adverse event should strictly follow the standard operating requirements to prevent accidents.

Pre- and post-treatment of each treatment session, the researchers will review the patient's symptoms according to the following safety classification:

Level 1: Safe, without any adverse reactions and treatment can continue.Level 2: Relatively safe, with minor adverse reactions, treatment can be continued without any additional remedial treatment for the injury.Level 3: There are safety problems, moderate adverse reactions, and treatment can continue after treatment of the injury.Level 4: Suspension of participation in research due to adverse reactions.Adverse events such as changes in pain, syncope, vertigo, and lumbar function degradation, will be carefully recorded in the case report form.

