### Suspension criteria

2.6

Subjects may discontinue from the study after discussions with the clinicians for the following reasons:

(1)The subject has an adverse reaction to the intervention.(2)The subject's pain score decreased to 0.(3)The subject wishes to withdraw from the clinical study.(4)The subject wishes to attend other interventions, which may result in the study bias, such as attending chiropractic or other massage therapy or non-traditional spinal treatment.

Those who meet any of the above suspension criteria shall be suspended. However, all subjects’ responses will be recorded to determine the reasons for suspension from the study and the intention-to-treat analysis.

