### Blinding

2.9

Due to the inability to blind patients, the practitioners, physiotherapists, and patients are not blinded.

The assessment of clinical efficacy will be performed by a clinical assessor who will be masked to the treatment assignment. The clinical researcher, assessor, and statistician do not share study information during this clinical trial.

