### Statistical analyses

2.16

The analysis set will consist of a full analysis set (FAS), a per-protocol set, and a safety set. The safety set will include randomly assigned participants and receive at least one intervention treatment. The FAS will consist of data indicating that the treatment was as close to the intention to treat as possible. In addition to meeting the safety set criteria, the participants must have been evaluated for the primary outcome at least once at the baseline. The FAS will be used in the primary analysis. For missing data, we will analyze the underlying reason and use an imputation adjustment approach, and the last observation carried forward analysis will be used to handle the missing data. After the primary analysis, a sensitivity analysis will be performed by comparing the results from the per-protocol analysis and the intention to treat analysis to evaluate the impact of missing data on the trial results. Besides, subgroup analyses by the center will be done.

(1)Statistical analysis methodFor all of the analyses, SAS version 9.4 was used. The confidence interval will be established at 95%, and the significance level at 0.05.Continuous variables were analyzed with an ANOVA test if normally distributed (results are presented as means ± SD) or Kruskal-Wallis H test if not normally distributed (presented as median with interquartile range). Multiple comparisons were addressed using the Tukey post hoc test (for ANOVA), and Bonferroni correction (for Kruskal–Wallis). The classification count data is checked by the chi-square test. This study used a one-sided test. When *P* < .05, the difference was considered statistically significant.(2)Statistical analysis contenta.Baseline evaluation: Social demographic characteristics, baseline severity analysis.b.Efficacy evaluation: We use the low back pain VAS score sheet, spinal ROM sheet, ODI scale, SF-36 scale, and the number of treatment sessions.c.Safety evaluation: Evaluation was made by the incidence of adverse events or recurrence of pain, or further injury from accidents during the follow-up period, and the level of safety.d.Compliance evaluation: Evaluation was carried out using the compliance rate.

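### The safety level in section 2.12 switches from grading the reaction (Levels 1–3) to recording suspension (Level 4), so the level of safety evaluated in section 2.16 mixes severity with the decision to stop

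*Protocol article*

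**What the plan says.** All references are to the protocol article. Section 2.12 (Safety evaluation) has the researchers review symptoms before and after each session and assign one of four levels:

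- "Level 1: Safe, without any adverse reactions and treatment can continue"
- "Level 2: Relatively safe, with minor adverse reactions, treatment can be continued without any additional remedial treatment for the injury"
- "Level 3: There are safety problems, moderate adverse reactions, and treatment can continue after treatment of the injury"
- "Level 4: Suspension of participation in research due to adverse reactions"

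Section 2.12 also has adverse events entered in the case report form, and section 2.14 has them recorded for all subjects.

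Section 2.16, item (2)c, names the components of the safety evaluation. They are the incidence of adverse events, recurrence of pain, and "further injury from accidents during the follow-up period, and the level of safety".

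Section 2.6 (Suspension criteria) opens permissively: "Subjects may discontinue from the study after discussions with the clinicians for the following reasons". The first reason listed is an adverse reaction to the intervention, with no severity attached. The section closes by making suspension mandatory for anyone who meets any of the criteria. Section 2.9 (Blinding) says that "the practitioners, physiotherapists, and patients are not blinded".

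**The concern.** An ordered scale is useful when each step up means more of the same thing. Here the first three steps describe how bad the reaction was, together with what was done. The fourth describes only that the patient left because of a reaction. Two patients with the same minor reaction therefore get different levels if one leaves and the other stays. A patient with a worse reaction who is treated and stays gets a lower level than a patient with mild soreness who leaves.

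This matters because safety is part of the trial's stated purpose (end of the Introduction), and section 2.12 itself mentions possible muscle, bone or joint damage. The level is the only graded harm measure that the article defines. If readiness to leave after a reaction depends on the arm, which patients and therapists know, the distribution of levels can differ between arms without any difference in harm.

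**Working it through.** No figure in the article bears on this point, so the check sets the sections side by side.

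**Step 1. What each level fixes (section 2.12).**

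| Level | Reaction grade stated | Consequence stated |
|---|---|---|
| 1 | none | continues |
| 2 | minor | continues, no remedy needed |
| 3 | moderate | continues after the injury is treated |
| 4 | not stated | suspended |

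No level uses a term such as severe or serious.

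**Step 2. Apply the levels to two patients.**

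- *Minor reaction, patient leaves because of it.* Level 2 requires that treatment can continue, so it does not fit. Level 4 fits as worded, and section 2.6 allows the exit because its adverse-reaction criterion has no severity threshold. Result: the highest level for a minor reaction.
- *Severe reaction, treated, patient continues.* Level 4 does not fit because there is no suspension. By its consequence the case belongs at Level 3, where it is labelled moderate. Result: a severe reaction recorded one level below the minor reaction above.

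**Step 3. Who can influence the stop.** Section 2.6 places the decision in a discussion between subject and clinicians. Section 2.9 leaves patients, practitioners and physiotherapists unblinded. It follows, by inference, that the share leaving after a given reaction can depend on the arm.

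**Step 4. Mechanism in numbers (assumed rates; none are in the article).** With 1:1:1 allocation, n = 612 / 3 = 204 per arm. Let r be the reaction rate, equal in two arms, and s the share of reacting patients who leave because of it. The expected Level 4 count is n × r × s.

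| r (both arms) | s = 10% vs 30% | s = 20% vs 50% |
|---|---|---|
| 5% | 1.0 vs 3.1 | 2.0 vs 5.1 |
| 10% | 2.0 vs 6.1 | 4.1 vs 10.2 |
| 20% | 4.1 vs 12.2 | 8.2 vs 20.4 |

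For example, 204 × 0.10 × 0.20 = 4.08 and 204 × 0.10 × 0.50 = 10.2. If s is equal in the two arms, the difference vanishes. The table shows only that Level 4 can differ with identical reactions. It does not estimate how much it will.

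**Step 5. Section 2.6 against section 2.12.** If the mandatory closing sentence of section 2.6 is taken literally, every adverse reaction leads to suspension. Levels 2 and 3 are then empty, every reaction is Level 4, and the item carries no severity information. If the permissive opening governs, the two cases in Step 2 can both occur. The two sections cannot both be applied as written.

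**The case against.** The strongest reply is that the scale is really one of consequence: continue, continue without remedy, continue after remedy, suspended. On that axis it is ordered and has no gap. This stands in part. A reader might infer that a severe reaction in a continuing patient has no place on the scale at all. The text does not support that, because such a patient can be put at Level 3 by its consequence. What remains is that the label there is moderate, and that a level read as severity is wrong for both patients in Step 2.

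Second, harm is captured outside the scale. Adverse events are recorded (sections 2.12 and 2.14), and their incidence and later injuries are evaluated next to the level (section 2.16). A reader might infer that an arm with severe but tolerated injury would appear free of harm. That does not follow; only its Level 4 count would be empty. Incidence as described in the article carries no severity, however, so it does not replace the grade.

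Third, section 2.16 lists the level as an item of evaluation and does not say that it is tested between arms. Comparison by arm is the natural reading in a three-arm trial, but it is an inference. So is the unblinded stopping decision: section 2.12 does not say whether the researchers who assign the level are blinded.

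Fourth, the case report form and the full protocol are not shown and may hold a severity field. That could make the fix easier, but it would not change the printed definition of the level.

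Finally, separating the two items does not remove bias from judging severity without blinding. That is correct, and the fix does not claim to.

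**Conclusion.** The point holds in a limited form. As printed, the level of safety mixes the severity of a reaction with the decision to stop. It puts a minor reaction followed by exit at the highest level, and a severe reaction in a treated, continuing patient at a level labelled moderate. The first result follows directly from sections 2.6 and 2.12. The second assumes that such a patient continues, which the permissive wording of section 2.6 allows and its mandatory wording does not. That the mixture can differ by arm rests on the inference from sections 2.6 and 2.9.

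The defect is confined to the graded item. It does not touch the primary outcome or the separately evaluated incidence of adverse events. No size can be derived from the document, and the counts in the working are illustrations on assumed rates. The change is worth making because it is cheap and stops a stated rule from misgrading harm.

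**What to change.** At the session review already planned in section 2.12, record two items in place of one:

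- severity of the reaction: none, minor, moderate, severe;
- action taken: none, injury treated, participation suspended.

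In section 2.16, item (2)c, base the level of safety on the severity item, and report suspension due to adverse reactions as its own count by arm.

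The cost is one case report form field and a short edit to sections 2.12 and 2.16. Severity remains a judgement that may be made unblinded, so the article should say who makes it. The change concerns classification and analysis only and does not alter when treatment stops.

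Separately, sections 2.6 and 2.12 must be reconciled on whether a patient with an adverse reaction continues or is suspended. That choice is clinical, and no stopping rule is proposed here.

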### Follow-up

2.13

To evaluate the interventions’ short-term efficacy and safety, we will follow up with participants for 3 months after the trial. In the 20th week, the outcome assessor will telephone participants to investigate their low back pain recurrence. Patients can also inform the assessors of their clinical symptoms and AEs face to face or by email, text message, or WeChat.

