### Data collecting and monitoring

2.14

All baseline assessment, end of 2-month intervention, 3 months post-intervention data will be collected by the CRC blind to the treatment modality or treatment groups. All subjects’ adverse events and additional treatment during the follow-up period will also be recorded.

This trial uses a paper-based case report form (CRF) and an electronic data management system. All data will be recorded by CRC in CRFs. Completed CRFs are reviewed by Clinical Research Associate (CRA), from a third-party company, independent of the research team and blinded to group allocation. All data administrators have data analysis qualifications and are trained uniformly. To ensure the accuracy of the data, 2 data administrators independently enter the information and proofread it. If there are issues with the information in the CRF, the CRA can fill out a query sheet and give it to the CRC and site PI. The CRC can then modify the data according to any revisions made by the site PI. After confirming that the database is correct, the site PI, CRC, and statistician will lock the database.

All documents that contain participants’ personal information will be identified by code number and stored separately. Only researchers involved in this study can be available to the confidential documents.

All study data, including the paper-based documents and electronic data, will be stored at each site for 5 years after the completion of the trial.

Because the study is not a drug trial and the sponsor or funder has no access to the raw data, a data monitoring committee will not be formed, and there is no planned trial audit. Besides, there are no interim analyses and stopping guidelines due to the very low risks of adverse events and other unintended effects.

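### Patient reports go straight to the masked assessor, and the blinded coordinator records all CRF data: an avoidable risk to masking, mainly in follow-up

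*Protocol article*

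**What the plan says.** Section 2.9 (Blinding) states that "the practitioners, physiotherapists, and patients are not blinded". Against that it sets one protection at the point of measurement: "The assessment of clinical efficacy will be performed by a clinical assessor who will be masked to the treatment assignment". The supporting rule is that "The clinical researcher, assessor, and statistician do not share study information during this clinical trial".

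Section 2.13 (Follow-up) gives the assessor a direct role with patients after treatment: "In the 20th week, the outcome assessor will telephone participants to investigate their low back pain recurrence". It then opens a second, patient-initiated route: "Patients can also inform the assessors of their clinical symptoms and AEs face to face or by email, text message, or WeChat".

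Section 2.14 (Data collecting and monitoring) says that data at baseline, end of treatment and 3 months after it "will be collected by the CRC blind to the treatment modality or treatment groups". In the next paragraph it says "All data will be recorded by CRC in CRFs". The same section adds that adverse events and additional treatment during follow-up are recorded, and section 2.12 (Safety evaluation) places adverse events in the CRF.

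**The concern.** Patients and therapists are open to treatment here, so masking of the assessor and of the analyst is the only blinding the design has. Assessor masking can protect what an observer measures or judges: spinal range of motion, the recurrence enquiry at week 20, the recording of adverse events, and the way questionnaires are administered.

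The procedures in sections 2.13 and 2.14 pull against it. An unblinded patient describing symptoms or a reaction in free form, after hands-on treatment, may well mention what was done. The article names the masked assessor as the recipient of such accounts. It also gives one role, described as blind to modality, the recording of every CRF item, with no separation of safety and treatment data from outcome data.

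If the arm becomes known, later judgements by that person can drift towards expectation, and the report could not then describe those outcomes as assessed blind without qualification.

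**Working it through.** No arithmetic applies: the point concerns who receives and records what, and it depends on no sample size, power or significance level. The check is to set the statements side by side.

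1. **Who knows the arm.** Patients, practitioners and physiotherapists (section 2.9).

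2. **Who must not know it.** The efficacy assessor (section 2.9) and the CRC (section 2.14: "3 months post-intervention data will be collected by the CRC blind to the treatment modality or treatment groups"). The article does not say whether these are the same person; the point holds either way, since both are described as masked.

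3. **What the stated safeguard covers.** The rule in section 2.9 concerns information passing between the clinical researcher, the assessor and the statistician. Information passing from patient to assessor lies outside it.

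4. **What the plan routes to the masked roles.**
   - To the assessor: the week-20 call, and free-form symptom and adverse-event reports in person or by message (section 2.13).
   - To the CRC: all CRF data (section 2.14), which take in adverse events (section 2.12) and additional treatment during follow-up (section 2.14).

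5. **When the patient-initiated route operates.** It stands in the follow-up section. Treatment lasts 8 weeks and the call is in week 20, so the call comes 20 − 8 = 12 weeks after treatment ends. The primary outcome in section 2.11 is VAS change over the 2-month treatment. If the route is used only in follow-up, that outcome has already been collected.

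6. **Which results are exposed.** The recurrence enquiry and adverse-event incidence, both of which enter the safety evaluation in section 2.16, and any other assessment at 3 months. Whether range of motion is measured at 3 months cannot be read from the text, because the schedule figure is not available here. The CRC's recording role is not confined to follow-up, so it could reach end-of-treatment measurements too, but only if the pages handled by the CRC show the modality. The article does not say whether they do.

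7. **What the reports reveal by themselves.** The adverse events listed in section 2.12 are not tied to one arm. Disclosure would come through what the patient adds, not through the event type.

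Result: sections 2.13 and 2.14 create a route to disclosure that the safeguard in section 2.9 does not close. They do not state that the arm will be disclosed.

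**The case against.** The strongest reply is that reporting a symptom is not reporting an allocation. Every trial with open patients and a masked assessor carries some risk of disclosure, because each assessment is a contact with the patient. Section 2.13 adds opportunity rather than contradicting section 2.9. The per-session safety review in section 2.12 is done by the researchers, who are not identified with the assessor. The layout of CRF pages, access to them and instructions to patients are details that a journal article usually leaves to the full protocol.

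Much of this stands. A reader might infer that the procedures cancel the assessor blinding; the documents do not support that, because they describe a channel and not a disclosure. A reader might also infer that the number of sessions recorded in the CRF gives the arm away; section 2.10 plans 6 sessions of 30 minutes for all participants, so a count does not identify it. Nor can the risk be turned into an inflated error rate. That would need an average assessor shift across a whole arm, for which the documents give no value, and it would not describe the patient-rated primary outcome.

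The appeal to the condensed format does not dispose of the point. The complaint is not that a safeguard goes unmentioned. The article affirmatively names the assessors as recipients of patient reports and gives the blinded CRC all the recording. A full protocol that routed these elsewhere would disagree with the published text.

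**Conclusion.** The concern holds as a risk to masking that is avoidable and cheap to reduce. It falls mainly on the week-20 recurrence call, other 3-month assessments and follow-up adverse-event recording. The 2-month primary VAS is little affected: patients who know their treatment score it themselves, so assessor masking gives it limited protection in any case, and the patient-initiated route opens after it is collected.

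The size cannot be estimated from the documents, and no planned figure changes. The conclusion assumes that some patients will use the route and mention their treatment, which is plausible but not stated, and that the follow-up route is not used during treatment. The CRC part carries less weight than the assessor part, because the article leaves open whether the pages concerned show the modality.

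**What to change.** Reconcile sections 2.9, 2.13 and 2.14 as follows:

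- Send patient-initiated symptom and adverse-event reports to a site member who is already unblinded and is not the assessor. This should preferably not be the treating therapist: section 2.12 attributes possible injury to misused technique, and the person who applied the technique is a poor sole recipient of such reports.
- Have adverse-event and treatment pages of the CRF completed by someone other than the person who collects outcomes.
- Tell patients not to mention their treatment to the assessor, and repeat this at the start of the week-20 call.
- Record any unblinding of the assessor or CRC, with its date, so that affected assessments can be identified.

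The cost is revised wording, a contact point and a divided CRF. The small downside is that two people complete parts of one patient's form. Whether the sites can do this with existing staff is not something the article shows. Sample size and analysis are unchanged.
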